### Data collection

The managing team of each centre or department will be contacted to introduce the study and its objectives. When the administration of the centre authorises participation in the study a member of the research team will go to each of the PHC to inform the professionals, motivate them and invite them to participate. The questionnaires will be given and collected in a specific session in each PHC. One person in each PHC will be responsible for the administration and collection of the questionnaires from the professionals who are absent on the day of the session to be thereafter sent to the research team within a maximum time of two weeks for later processing and analysis of the data collected. The questionnaire to the professionals will be anonymous and self-administered. It will only have a code indicative of the team to which the health professional belongs to obtain the rate of response from each centre. At no time will the data obtained be able to identify the responding professional. Neither will data processing and analysis be able to identify the centres since they will be indexed with an alpha-numerical code with no relationship to the geographic location or service providing entity.

To administer the questionnaires to the families, cultural mediators from the healthcare centres will collaborate. These mediators will introduce the interviewer and will accompany them throughout the whole process of completing the questionnaire to clarify any concept or doubt in relation to the same which may come up among the families surveyed. The participating mediators are experts with specific training in intercultural mediation. For this study they will be instructed as to the characteristics of the questionnaires and the objectives and methods of the study. They will be trained in giving the questionnaire and the objectives sought with each of the questions will be explained. The questionnaire will always be given under the supervision of a member of the investigative team. The questionnaire to the families will be anonymous but hetero-administered. Information regarding the families who refuse to participate in the survey will also be collected.

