Types I and II are predominant in Western and Central sub-Saharan African countries, whereas type III is the most common form of FGM in Eastern Africa. It should be specified that not all African countries practice FGM, and neither is it practiced by all the ethnic groups in one and the same country. It is pre-Islamic and is practiced by Muslims, Coptic Christians and Falasha Jews.

The performance of FGM has an impact on the physical, psychic, sexual and reproductive health of women, severely deteriorating their present and future quality of life [7-13].

The social and cultural roots of these practices condition their perpetuation, despite important restrictive legal initiatives having been developed in some countries of origin and destination of the immigrants.

In addition to the many initiatives of the international agencies, who recommend their prohibition (WHO, UNICEF, UNFPA, EU), FGM in any of its forms is considered as a crime of injury in Spain, being described and punished in article 149 of the Penal Code with sentences of 6 to 12 years in prison even if the mutilation has been performed abroad.

On the other hand, the lack of intervention by healthcare professionals to avoid genital mutilation in situations of risk is considered to be a crime of omission of duty to avoid and promote persecution in article 450 of the Spanish Penal Code. This means, for example, that professionals who, in relation to their work activity, are aware of FGM having been performed or of a girl at risk of being submitted to this practice and do not avoid or report the event, are committing a crime which may be punished with a prison sentence.

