### Study variables

The questionnaire to the healthcare professionals will assess knowledge on FGM, attitudes and skills in approaching this problem in relation to the following areas:

• Sociodemographic data and of the professional setting: age, gender, professional category, work centre or department.

• Assessment of knowledge on: typology of FGM, cultural origin, geographic distribution and ethnicity of FGM, legal implications, consequences for the health of the women, formation received.

• Assessment of the attitudes of the professionals in relation to: beliefs regarding FGM, professional interest in relation to FGM, convenience or need to act on this problem, fears or insecurity generated on considering this subject, availability of preventive interventions, negativity towards immigrant patients, attitude toward judicial interventions related to FGM and their implications.

• Agreement or disagreement of the professional towards the response or actions to be undertaken in a situation of risk for a girl or towards a recent FGM.

• Previous contact with cases of FGM or situations of risk and previous experiences.

Similarly, the questionnaire for the families will include the following areas:

• Sociodemographic data: age, gender, country of origin, ethnicity, years of residence in Spain, number of children. Position of the different members of the family towards FGM.

• Knowledge of the consequences which FGM may have on the health of a girl.

• Knowledge of Spanish legislation and of the country of origin regarding FGM and the consequences of its practice, experiences (acceptation or rejection) related to the criminalisation of this practice.

• Position (acceptation or rejection) towards a possible preventive action on behalf of the healthcare professionals in Spain.

• Expectations towards the proposal of a preventive intervention aimed at their communities of origin, consequences of not performing FGM in relation to the community in both the country of origin and destination (diaspora), acceptation of alternative rituals to FGM.

Sociodemographic data (age, gender, ethnicity, country of origin, years of residence in Spain and number of children) will be collected from the sub-Saharan healthcare users who do not wish to complete the questionnaire, with the aim of detecting possible differences between users who accept and refuse to participate in the study.

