
### Ethics

This is a questionnaire for professionals who will be verbally informed as to the objectives and content of the questionnaire prior to being interviewed in their work centres. Participation is voluntary. Data analysis will remain totally anonymous to make identification of the participating professionals through their answers impossible. Neither will professionals who decide not to participate be identifiable. No direct intervention will be made (pharmacologic, educative, formative or preventive) in patients or healthcare users or in professionals except for knowing their opinions. The questionnaires for the families will be hetero-administered through a cultural mediator and will not include any information which will allow identification of the person interviewed. The questionnaire will be given in a specific room of the centre to ensure confidentiality and privacy for the participants. Data analysis will remain totally anonymous to make identification of the participating migrant people through their answers impossible. All the databases generated will retain adequate anonymity. Informed consent will be requested from participants in the study. In the case of migrant people, cultural mediators may be required to obtain this informed consent. The management personnel of the centres will be informed of the undertaking of the study and the study has been approved by the ethical committee of the Clinical Research Ethics Committee of the Primary Care Research Institute IDIAP-Jordi Gol (Barcelona, Spain).

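### The guarantee that professionals can never be identified is stronger than the questionnaire and the collection of absentees' forms can deliver

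*Protocol article*

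**What the plan says.** Three parts of the protocol article bear on this.

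- **The promise.** Data collection: "At no time will the data obtained be able to identify the responding professional". Ethics: "Data analysis will remain totally anonymous to make identification of the participating professionals through their answers impossible", and on those who decline, "Neither will professionals who decide not to participate be identifiable".
- **What the form holds.** Data collection: "It will only have a code indicative of the team to which the health professional belongs to obtain the rate of response from each centre". Study variables lists, for the same questionnaire, "Sociodemographic data and of the professional setting: age, gender, professional category, work centre or department". The Analysis plan crosses the professional items with each of these four variables, so they stay in the analysis file. Data collection adds that centres are indexed by an arbitrary alphanumeric code unrelated to location or provider.
- **How forms come back.** They are given out and collected in a session at each centre, which a member of the research team visits. For those who miss it, "One person in each PHC will be responsible for the administration and collection of the questionnaires from the professionals who are absent"; the forms then go to the research team within two weeks.

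On the subject matter, the Background says that a professional's failure to intervene against a threatened mutilation "is considered to be a crime of omission of duty to avoid and promote persecution in article 450 of the Spanish Penal Code". The questionnaire covers previous contact with cases or risk situations, previous experiences, and agreement or disagreement with actions to be taken.

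**The concern.** Removing names does not make a form unidentifiable. Team, category, gender and age together can single out one person to somebody who knows the team, and the protocol places all of them on one form. The promise is absolute, so a single recognisable respondent is enough to break it.

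Two things are at stake. The first is the accuracy of what professionals are told before they take part. The second is candour. A respondent who sees these items, on a subject the article itself ties to criminal liability, may be less willing to report cases met or to disagree with the legally expected response. That would touch the practice results (objective 1), the dilemma results (objective 3) and the frequency of case contact (objective 5).

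**Working it through.** The article gives no figure for identifiability, so there is none to reproduce. The check has two parts.

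**1. The text set side by side.** Data collection says a team code is the only marker. Study variables adds age, gender, category and work centre or department, and the Analysis plan retains them. The arbitrary centre code hides the centre from an outsider. It does not hide it from whoever handles the forms in the centre, nor from whoever matches codes to centre staff counts, which the response rate per centre requires. The person who collects absentees' forms necessarily sees which absentees returned one and, without sealed return, can read it.

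**2. How many would be unique in their team.**

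From the documents: 25 centres; team categories of family physicians, general medicine physicians, paediatricians, nurses and social workers, with gynaecologists, nurses and midwives in the support programmes.

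Not in the documents, so assumed:
- teams of 15 to 80;
- 75% women;
- age roughly normal, mean 45, SD 9.5, limited to 25 to 65;
- seven categories with shares 33, 5, 9, 40, 4, 4 and 5%, or three broad ones with shares 45, 42 and 13%.

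If a fraction p_k of staff fall in combination k of category, gender and age, the expected share of a team of T that is unique is

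Σ p_k (1 − p_k)^(T−1).

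Simulation with 2,000 teams per cell gives the following; the formula agrees to within one percentage point.

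| Age format | Categories | T = 15 | T = 30 | T = 60 | T = 80 |
|---|---|---|---|---|---|
| Years | 7 | 93% | 86% | 75% | 69% |
| Years | 3 | 90% | 80% | 66% | 58% |
| 5-year bands | 7 | 71% | 53% | 36% | 29% |
| 5-year bands | 3 | 62% | 41% | 22% | 17% |
| 10-year bands | 7 | 55% | 37% | 23% | 18% |
| 10-year bands | 3 | 44% | 24% | 12% | 8% |

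Small categories drive what remains after banding. Ignore age altogether and take a team of 30. A woman in a category holding 4% of staff is the only one of her kind with probability (1 − 0.04 × 0.75)^29 = 0.97^29 ≈ 0.41. For a woman in the 40% category it is (1 − 0.40 × 0.75)^29 = 0.70^29, effectively zero.

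The calculation counts uniqueness among all team members, so the response rate does not enter. Unique here means recognisable to someone who knows the staff; it does not mean named.

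**The case against.** The strongest reply is that the article describes a reasonable anonymous survey and the criticism is about wording.

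- **Collection.** Most forms are collected in a session at a centre that the research team visits. A reader might infer that every form passes through a colleague. The text does not support that: in-centre handling applies to absentees, and the person is not described as a colleague.
- **Most respondents unique.** A reader might infer this from the list of variables. It holds in every scenario tried only if age is in years. With 10-year bands it holds only in the smallest team with seven categories, and the article states neither age format nor team size.
- **Centre code.** It is a real safeguard against outsiders, and the work centre item may be that same code rather than a second entry.
- **Punishable omissions.** A reader might infer that the form asks staff to admit them. No item on past failure to report is listed, and the third objective concerns hypothetical presentations.
- **Bias.** None of the arithmetic measures it. The group's earlier surveys reached about 75% response by the same system, and in the earlier survey 17% were not interested and gave an unwelcome answer about what they would do. That suggests some candour, although the earlier form is not shown.
- **Readings and detail.** The promise about non-participants can be read as covering only the data, and the team code as the only administrative marker. Envelopes and cell rules are details an article may leave out.

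All of this limits the size of the point. It does not rescue the absolute promise, which the article makes expressly and which its own variables contradict under every assumption tried. The absence of envelope or cell-size rules is not counted as a fault; they appear below only as remedies.

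**Conclusion.** The point stands in a limited form. The design does not have the property claimed in Data collection and Ethics: some professionals could be recognised from their forms by someone who knows the team or holds the code list. The share runs from 8% to 93% across the scenarios, and it rests entirely on assumed team size, staff mix and age format. That the share is above zero does not depend on a particular choice among them.

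For absentees, one person in the centre can see who returned a form. This sits badly with the promise about non-participants, unless that promise is confined to the data.

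Loss of candour is a plausible consequence given the legal context, but it is neither shown nor sized. The matter should be corrected before fieldwork; it does not undermine the study.

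**What to change.** 1. Use the team code as the only centre identifier on the form. Comparisons by work centre or department can be made from it.
2. Record age in bands. Under the assumptions above, 10-year bands cut the unique share in a team of 60 with seven categories from 75% to 23%.
3. Have every form returned in an unmarked sealed envelope, both in the session and by absentees.
4. Suppress small centre-by-category cells in reports.
5. In Data collection and Ethics, replace the absolute wording with a statement that no direct identifiers are collected, followed by the steps taken. Banding leaves some staff in small categories unique, so the present wording cannot be kept even with steps 1 to 4.

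Keep professional category and team code as planned. Category is a factor in the bivariate analyses, and the team code is needed for centre response rates and for the stratification by participation rate foreseen under sample size. Merging categories or pooling codes across centres would damage both.

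The cost is that age is analysed as an ordinal factor rather than in years, plus envelopes and a little extra handling.

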### Analysis plan

The quality of the data will be evaluated, treating extreme and rare values. Regarding the questionnaire to the healthcare professionals, to answer the first and second objective, each of the issues included in the area of assessment of knowledge (typology of FGM, cultural origin, geographic distribution and ethnicity of FGM, legal implications, consequences for de health of the women and formation recived) and included in the area of assessment of the attitudes of the professionals (beliefs regarding FGM, professional interest in relation to FGM, convenience or need to act on this problem, fears or insecurity generated on considering this subject, availability of preventive interventions, negativity towards immigrant patients, attitude toward judicial interventions related to FGM and their implications) will be described for univariate analysis, mean and standard deviation for quantitative variables and frequency and percentage for qualitative variables. Then a bivariate analysis will be performed between each of the above issues and gender of the healthcare professionals, age, professional category and work centre or department. To do this we will use different tests adequate to the type of data. To answer the third objective, we will do the same as the first and second objective but with each of the issues in the area of agreement or disagreement of the professional towards the response or actions to be undertaken in a situation of risk for a girl or towards a recent FGM. To quantify the frequency of presentation of problems related to FGM in primary care offices (fifth objective), we will do the same as first, second and third objectives but with each of the topics in the area of previous contact with cases of FGM or situations of risk and previous experiences. By analyzing all this information, and mainly from the results obtained with the area of assessment knowledge, we will be able to identify the training needs of the primary care professionals in relation to how to approach FGM, providing a good answer to the fourth objective. A multiple logistic regression model will be used to assess the characteristics of the professionals associated with correct identification of FGM (types that exist, countries in which it is performed, health consequences, reasons for implementation and prosecution by law). Regarding the questionnaire for the families, to describe the sample of immigrant families, each of the issues of the areas of the study will be described for univariate analysis, mean and standard deviation for quantitative variables and frequency and percentage for qualitative variables. To answer the last objective (sixth objective), bivariate analysis will be performed between the area of sociodemographic data and the remaining areas of study to evaluate possible differences between men and women, young persons and the elderly, based on the country of origin, ethnicity, years of residence in Spain and the number of children, with regard to knowledge of the consequences on health which FGM may imply, knowledge of legislation, position towards a possible preventive action on behalf of the healthcare professionals, expectations towards the proposal of a preventive intervention aimed at their communities of origin, consequences of not performing FGM in relation to the community in both the country of origin and destination, and acceptation of alternative rituals to FGM. Comparison between responders and non-responders immigrants will be performed using bivariate analysis to evaluate possible differences in participation between men and women, young and the elderly, based on the country of origin, ethnicity, years of residence in Spain and based on the person who proposed their participation in the study. This will be performed with tests according to the type of distribution and type of variables. Moreover, a multiple logistic regression model will be used to assess the characteristics associated with a possible preventive acceptance by immigrant families. The criterion of statistical significance will be p < 0.05.

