There are few studies in Spain related to FGM in primary care. A previous survey carried out by investigators of our team of healthcare professionals in the county of the Maresme (Barcelona) [14,15] reported that 56% of those surveyed did not correctly identify the typology of FGM, 17% were not interested in the subject and their answer to the question "What would you do in the case of FGM?" was: "ignored". Twenty-one percent of the personnel of the sexual and reproductive healthcare programme, 7% of the paediatricians and 5% of the general medicine professionals declared having detected or known of some case in both mothers and daughters. This study demonstrated the profound lack of knowledge of the healthcare professionals in relation to this subject, raising the need to sensitise and educate from the privileged setting of primary healthcare, where most of the cases or situations at risk are detected. In other European countries the situation is similar [16-18].

The important migratory waves of sub-Saharan populations to the European Union in the last years are shaping societies which are increasingly more complex and diverse. The way to deal with the health problems affecting these people represents a challenge for the healthcare systems [19] and for the professionals working within who must develop approaches to allow transcultural care [20-22].

Based on the production of mapping FGM in Spain, with data of the census and municipal registration, updated in 2005 we have estimated that 3,659 women living in Catalonia have undergone some type of FGM; and 2,189 girls are at risk of having some type of FGM performed in the next years, without taking into account the impact of the last processes of immigration regularisation.

The deep-rooted social and cultural nature of these practices conditions their perpetuation despite the development of important legal restrictive initiatives in some countries of origin and destination of the immigrants. However, when migrant women return to their societies of origin they are points of reference, credibility and recognition in such transcendent aspects as reproductive health and education [23]. These women bear new knowledge acquired in Europe which has been incorporated and put into practice during the migratory process. Thus, the exploration of the beliefs and perceptions of the sub-Saharan immigrants attending our healthcare centres in relation to FGM may be of interest.

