Sample size: According to the last municipal registry data available (11% of the immigrant population, 13.5% of which is of sub-Saharan origin), the population eligible in our study area is of 7,200 individuals. We assume that the prevalence of FGM in most of these countries is above 80% according to the reports of international organisations [6]. With an alpha risk of 0.05% for a precision of ± 0.06 percentual units and assuming 10% of non-responders, a sample of 191 subjects is required.

Non responders: a questionnaire will be elaborated for the immigrants selected who refuse to participate in the study. This questionnaire will collect only sociodemographic data, country of origin, etnia, years of residence in Spain and the reason for refusal to participate as well as the name of the person who proposed their participation in the study (interviewer, mediator or both). The aim of this questionnaire is to identify differences between the responder and non responder immigrant populations.

With respect to the healthcare professionals, the different rates of participation in the Primary Healthcare Centres will be taken into account in the analysis. Thus, if necessary, the principal results will be stratified according to the rate of participation.

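### Previous contact with FGM cases is compared by gender and age with crude tests only, so a difference between professional categories may appear as a gender or age difference

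*Protocol article*

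**What the plan says.** All statements are in the protocol article.

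- **Knowledge and attitudes (Analysis plan).** After univariate description, bivariate tests are run one characteristic at a time, "between each of the above issues and gender of the healthcare professionals, age, professional category and work centre or department".
- **Actions, objective 3.** The scheme is repeated: "we will do the same as the first and second objective but with each of the issues in the area of agreement or disagreement".
- **Previous contact, objective 5.** It is repeated again: "we will do the same as first, second and third objectives but with each of the topics in the area of previous contact".
- **Multivariable analysis of professionals.** One model is named, for a knowledge outcome: "A multiple logistic regression model will be used to assess the characteristics of the professionals associated with correct identification of FGM". Its covariates are not listed.
- **Stratification of professionals' results (end of the sample-size text under Immigrant families).** The only form foreseen is by centre participation: "if necessary, the principal results will be stratified according to the rate of participation". Stratification by professional category is not mentioned.
- **Earlier evidence on contact (Background).** In the team's previous survey, "Twenty-one percent of the personnel of the sexual and reproductive healthcare programme, 7% of the paediatricians and 5% of the general medicine professionals" reported having detected or known of a case.

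The significance criterion for all tests is p < 0.05.

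**The concern.** Professional category is strongly related to contact in the authors' own data. It is also a variable that can be tied to gender and age, because staff groups need not have the same composition. A crude comparison of contact between women and men, or between younger and older staff, then mixes two things: any difference within a category, and the difference in category make-up between the groups compared. The planned tests cannot separate them.

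The plan fits a multivariable model for correct identification, and another for families' acceptance of prevention. It fits none for contact, the outcome for which the article itself shows a large category gradient. At stake is interpretation: a significant crude result could be reported as an association with gender or age when it reflects where people work. The distortion can also run the other way and hide a real difference within categories.

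**Working it through.** The plan gives no figure for this comparison and no expected number of professionals, so there is no stated result to reproduce. The check asks how far a category gradient alone can move the crude gender comparison.

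**Inputs from the document.** Contact: 21% in sexual and reproductive health (SRH), 7% in paediatrics, 5% in general medicine (Background).

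**Assumed inputs, not in the document.** The share of staff in each category, the share of women in each category, and the total number of respondents N. The three groups are treated as the whole workforce, although nurses and social workers have no separate contact figure.

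**Step 1: strength of category.**
- SRH against general medicine: risk ratio 0.21/0.05 = 4.2; odds ratio (0.21/0.79)/(0.05/0.95) = 5.05.
- SRH against paediatrics: risk ratio 0.21/0.07 = 3.0; odds ratio (0.21/0.79)/(0.07/0.93) = 3.53.

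**Step 2: crude rates with no gender effect inside any category.** With category share m, share of women f and contact rate r:
- women: Σ m·f·r / Σ m·f
- men: Σ m·(1−f)·r / Σ m·(1−f)

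In each line below the order is SRH / paediatrics / general medicine.

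*Equal mix.* Staff 15/15/70%, women 80/80/80%. Both rates are 0.15×0.21 + 0.15×0.07 + 0.70×0.05 = 7.7%. Odds ratio 1.00.

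*Mild imbalance.* Staff 10/15/75%, women 90/70/70%.
- Women: (0.09×0.21 + 0.105×0.07 + 0.525×0.05)/0.72 = 0.0525/0.72 = 7.3%.
- Men: (0.01×0.21 + 0.045×0.07 + 0.225×0.05)/0.28 = 0.0165/0.28 = 5.9%.
- Odds ratio 1.26; difference 1.4 points.

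*Intermediate.* Staff 15/15/70%, women 95/80/60%.
- Women: (0.1425×0.21 + 0.12×0.07 + 0.42×0.05)/0.6825 = 0.0593/0.6825 = 8.7%.
- Men: (0.0075×0.21 + 0.03×0.07 + 0.28×0.05)/0.3175 = 0.0177/0.3175 = 5.6%.
- Ratio of the two rates 1.56.

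*Strong imbalance.* Staff 20/20/60%, women 98/80/50%.
- Women: (0.196×0.21 + 0.16×0.07 + 0.30×0.05)/0.656 = 0.0674/0.656 = 10.3%.
- Men: (0.004×0.21 + 0.04×0.07 + 0.30×0.05)/0.344 = 0.0186/0.344 = 5.4%.
- Odds ratio 2.00; difference 4.8 points.

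In every case the category-adjusted odds ratio is 1.00 by construction. All the uneven mixes assume that SRH is the most female group; the opposite imbalance would push the crude odds ratio below 1.

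**Step 3: chance that the crude gender test gives p < 0.05 (two-sided assumed).** Over the uneven mixes examined, from the mild to the strong case above, it is about 5–28% at N = 300, 8–52% at N = 600 and 11–76% at N = 1000. With an equal mix it is the nominal 5%.

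No corresponding calculation was made for age. The mechanism is the same, but its size would need an age mix by category.

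**The case against.** The study is declared transversal and descriptive, and objective 5 is to quantify frequency. A crude percentage of contact by gender is a correct description and misleads only if read as an effect of gender. Category is itself a planned comparator for every item, so its gradient would be visible beside any gender difference. The article gives no gender or age mix by category. Finally, a condensed article may leave further models to a fuller document, and the text does not rule them out.

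Much of this stands. The crude tables should be kept, and the distortion is a possibility, not a prediction. Two parts do not settle the matter. The plan goes beyond percentages by testing each item against gender and age at p < 0.05, and separate tables for category and gender do not show whether the gender difference persists within category. Nor is the article merely silent: it assigns methods area by area and gives contact the bivariate scheme.

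A reader might infer two stronger points that the documents do not support:
- **That attitudes and intended actions are confounded in the same way.** This is plausible, but the 21%, 7% and 5% concern contact only, for three groups in one county.
- **That training would be aimed at the wrong groups.** The Analysis plan draws training needs mainly from the knowledge results, where correct identification has a multivariable model, and nothing says training will be targeted by gender or age.

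**Conclusion.** The point holds for contact, as a conditional risk. Two facts come from the article: contact is compared with gender and age by crude tests only, and contact differed 4.2-fold between professional categories in the team's earlier survey. Whether the crude tests mislead depends on a gender or age mix by category that the article does not report. With no gender effect within categories, the crude odds ratio is 1.00 under an equal mix and about 1.3 to 2.0 under the assumed uneven mixes. That range also rests on assumed category shares and on the earlier contact rates carrying over to this study. It is a modest improvement to the analysis and does not invalidate the descriptive results.

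**What to change.** - Keep the crude tables by gender and age, and label them as unadjusted description.
- For the previous-contact items, also report gender and age associations adjusted for professional category. Use the logistic model type already planned "to assess the characteristics of the professionals associated with correct identification of FGM", or Mantel-Haenszel stratification by category.
- Apply the same rule to any attitude or action item for which a gender or age difference is to be interpreted, and state this in advance. Items that are only tabulated need no model.
- Show the gender and age distribution by category, so that readers can judge how much adjustment matters.

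Gender, age and professional category are already collected, so the cost is a few extra models. The drawback is imprecision where a category has few men. Under the intermediate mix, men in SRH are 0.15 × 0.05 = 0.75% of staff, or 4 to 5 people among 600 respondents. Report confidence intervals and, where a category is too sparse for a within-category comparison, say so.
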